### Data Collection

De-identified information will be collected and managed by assigning an identification code to each participant. Demographic information, medical history, any occurrence of adverse events, practice adherence and intervention outcomes during the study will be collected and recorded on paper or electronic file.

Demographic information and medical history will first be collected by the Researcher. De-identified Practice Diary, Brief Fatigue Index, Pittsburgh Sleep Quality Index, and Centre for Epidemiologic Studies Depression will be collected at Week-1, Week-6, Week-12, and Week-16, while the 24-hour urine cortisol results will be collected by the research assistant at Week-1 and Week-12. Interviews will be conducted by the Researcher after Week-16, audio-recorded, de-identified, and transcribed verbatim.

During the study, all data will be recorded in participant source document files in paper format (sociodemographic data, feasibility and clinical data), administered by independent research assistants and will be transferred to an electronic format for storage and analysis. The 2 independent research assistants will verify and check the data collected by each other. After all data are confirmed and checked the research assistants will extract the data into an Excel sheet for analysis.

After participants have been randomized, dropout and premature termination or withdrawal from the 2 groups at any point will be recorded along with relevant reasons. Participants can choose to withdraw and will not be affected at any time while declining to participate or withdrawing from the trial. In some cases, participants will discontinue the intervention, such as illness, progression of their disease, or inability to engage despite adjustment of the program. Participants who withdraw from the intervention during the trial will not be replaced.

Interviews will be conducted after Week-16 in person or online via Zoom by the Researcher at an appointed time. Interview sessions will be audio recorded and transcribed verbatim using NVivo or the recording feature available in Zoom, ensuring accurate documentation, and stored in electronic files for analysis.

### Data Management

De-identified electronic data will be stored on a password-protected computer. Files will be accessible for review only to the research team. Specific requests will be needed from the supervisory panel for any access by any other person. All completed forms and study information will be de-identified and stored in a locked filing cabinet together with consent forms at UMMC.

The information collected will be securely locked and only accessible to the research personnel. The data will be de-identified for analysis and once date is coded, all identifiable information will be destroyed. All data collected in the study will be destroyed 7 years after publication.

## Data Analysis

### Quantitative Data

Data analysis will be conducted by an independent statistician. Data analysis will be by intention to treat using last observation carried forward (LOCF).^
93
^ The normality of the study data will be checked by examining the mean, median, skewness, and kurtosis including graphical representation of the box plot, normal Q-Q Plot or histogram. Continuous data will be summarized using descriptive statistics including the number of observations used in the calculation (*n*), mean, standard deviation (SD), minimum, median and maximum. Categorical data will be summarized as counts and percentages of each category. Between group comparison will be conducted using the t test, chi-square test, or Fisher exact test, as appropriate. We will report the results for two-sided 5% tests for the primary trial outcome. We will use generalized linear mixed model (GLMM). The outcomes of the model will be BFI, PSQI, CES-D scores, and 24-hour urine cortisol test results. Models will include the treatment group as a fixed effect, with time as a random effect to account for the repeated measurements. Analyses will be conducted to identify the baseline characteristics of the participants who may benefit most from the intervention. Model assumptions will be checked and appropriate adjustments to the analysis will be made where necessary. STATA^®^ software version 17.1 (2021; Stata Corporation, College Station, TX, USA) will be used for all analyses. Cohen’s D will be calculated as the absolute differences between the mean change in the variable divided by pooled variance of the change.

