It is feasible for cancer survivor participants to engage in the GQ training and those who participated in the GQ training will experience positive impacts on CRF, sleep, depression, and cortisol level. Feasibility of this study is established at about 80% to 85% retention rate and 75% to 85% class attendance rate based on prior similar studies.^63
[Bibr bibr64-15347354241252698]-65^The semi-structured interview will identify a broader spectrum of benefits and barriers to participation and adherence to GQ training to provide valuable insights for program enhancement.

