### Study Assessments

The variables under consideration will encompass basic demographic data, primary outcomes, and secondary outcomes. Basic characteristics will be collected at baseline (Week-1).

Primary feasibility outcomes on adherence, attendance, and any adverse events will be recorded throughout the intervention period from Week-1 to Week-12 in the practice diary by the participants. Secondary patient-reported outcomes on fatigue, depression, and sleep will be measured at baseline (Week-1), mid-intervention (Week-6), post-intervention (Week-12), and 4 weeks after completion of intervention (Week-16). Urine samples (for urine cortisol test) to assess 24-hour urinary cortisol will be collected a day prior to enrollment date and post-intervention (Week-12). Primary feasibility outcomes and secondary patient-reported outcomes will be assessed by an independent research assistant to minimize bias. A summary of the planned data collection is shown in Figure 2.

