^ The PSQI was reported to be a stable measure of sleep quality with high test-retest reliability and construct validity.^79,80^

c. Depression—Centre for Epidemiologic Studies Depression (CES-D)

The CES-D is a short self-reported 20-item scale^
81
^ to be administered to measure depression symptoms at baseline, mid-intervention, post-intervention, and follow-up. The CES-D shows very high internal consistency and adequate test-retest repeatability.^
81
^ The score is the sum of all items, and the maximum score is 60. Scores ≥ 16 on the CES-D is considered as having “depressed symptoms.” The cut off score of 12 has been validated with DSM-III criteria for clinical depression.^81,82^

ii. Cortisol biomarker: 24-hour urine cortisol

Urine sample will be collected at baseline (Week-1) and post-intervention (Week- 12).^
83
^ Participants are briefed on the urine collection procedure during assessment and advised to obtain the 2.5 L urine collection container from any nearby BP Laboratories before baseline (Week-1) and post-intervention (Week-12). We use 24-hour urinary cortisol as a non-invasive, integrated measure of cortisol stress hormone activity that could be collected in participants’ home environments. Participants are instructed to collect all urine for 24 hours from 8:00am a day prior to baseline (Week-1) and post-intervention (Week-12) to 8:00am the next mornings and to send the urine sample collected to the nearest BP Laboratories the next morning itself. If the 2.5L collection container is completely full, subjects are advised to use a clean mineral water bottle to collect any specimen in excess of the 2.5 L collection. If subjects are unable to collect all urine for any reason, their samples will be deemed inadequate and no urinary cortisol data will be recorded for these subjects.

The 24-hour urine cortisol test provides a more accurate estimate of overall cortisol secretion^
84
^ to assess urinary-free cortisol (UFC) over a 24-hour period and provides an index of (unbound serum cortisol) the total amount of cortisol released by the adrenals. The 24-hour collection time reflects the amount of cortisol that is released over a complete circadian cycle, which is a physiologically meaningful unit of time. An integrated mean of cortisol levels over a 24-hour period is thought to provide a moderately stable measure of adrenocortical output.^
85

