### Sample Size

Using a small effect size (0.2)^
65
^ rather than a medium effect size (0.5)^
64
^ to achieve a more conservative estimation, the sample size is 25 cases in each group with 90% power and two-sided 5% significance trial design.^
88
^ Allowing for a drop-out of about 20% based on previous studies,^89
[Bibr bibr90-15347354241252698][Bibr bibr91-15347354241252698]-92^ a total sample of 60 (30 in each group) would be required.

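### LOCF as the intention-to-treat method biases the secondary efficacy estimates even under completely random drop-out, in a direction set by drop-out by arm together with each arm's trajectory

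*Protocol article*

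**What the plan says.** The Quantitative Data section fixes the missing-data method: "Data analysis will be by intention to treat using last observation carried forward (LOCF"). It does not limit the rule to particular outcomes and names no other method. The same paragraph continues: "We will use generalized linear mixed model (GLMM"), with BFI, PSQI, CES-D and cortisol as its outcomes. Group is a fixed effect and time a random effect. The text does not say whether the model is fitted to observed or to carried-forward data. Cohen's d is defined there as the "absolute differences between the mean change in the variable divided by pooled variance of the change".

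Loss is expected. Sample Size reads: "Allowing for a drop-out of about 20% based on previous studies". The hypotheses at the end of the Background say: "Feasibility of this study is established at about 80% to 85% retention rate". No split by arm is given.

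Under Study Assessments, the patient-reported outcomes are "measured at baseline (Week-1), mid-intervention (Week-6), post-intervention (Week-12), and 4 weeks after completion of intervention (Week-16"). Cortisol has two time points; Data Collection says the "24-hour urine cortisol results will be collected by the research assistant at Week-1 and Week-12". For participants who cannot collect all their urine, the cortisol section says "their samples will be deemed inadequate and no urinary cortisol data will be recorded for these subjects".

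**The concern.** LOCF is unbiased only if outcomes stop changing when a participant leaves, and this protocol gives reasons to doubt that. Participants range from newly diagnosed to long-term survivors. Entry requires a fatigue severity score of at least 3, so regression to the mean in both arms is plausible. Data Collection lists illness and disease progression among the reasons for stopping the intervention. If such participants also leave follow-up, LOCF keeps scores from before the deterioration.

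Unequal loss between arms is a realistic risk. The trial is open-label with a waitlist control, and participants may opt out after learning their allocation.

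At 20% loss, about 6 of 30 participants per arm (0.20 x 30) would have a filled-in Week-12 value treated as a measurement. At stake are the effect estimates, standard errors and Cohen's d for all four secondary outcomes, which a later trial might rely on.

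**Working it through.** The plan gives no figure of its own to reproduce on this point. It gives no drop-out by arm and no expected trajectory, so the inputs below are assumptions, shown over a range.

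**Patient-reported outcomes at Week 12**

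Let C be the change common to both arms by Week 12 and E the true GQ effect, in SD units with negative meaning improvement. Half of each is reached by Week 6. Let dT and dC be the drop-out shares in GQ and control, completely at random. Half the leavers go before Week 6 (baseline carried, change 0) and half before Week 12 (Week-6 value carried, half the change). Each arm's LOCF mean change is then its true change times (1 - d) + (d/2)(1/2) = 1 - 0.75d, so

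LOCF difference = E(1 - 0.75dT) + 0.75C(dC - dT).

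With C = -0.6 and E = -0.50:
- 20%/20%: -0.50 x 0.85 = -0.425.
- GQ 30%/control 10%: -0.50 x 0.775 + 0.75 x (-0.6) x (-0.20) = -0.3875 + 0.09 = -0.298.
- GQ 10%/control 30%: -0.50 x 0.925 + 0.75 x (-0.6) x 0.20 = -0.4625 - 0.09 = -0.553.
- No true effect, unequal splits: 0.75 x (-0.6) x (-/+0.20) = +/-0.09.

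A simulation with these trajectories (20,000 per arm) gave -0.420, -0.289 and -0.555, and +0.099 and -0.106 under the null, in line with the formula.

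Range over the common trend, true effect -0.50:

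| Common change C | 20%/20% | GQ 30%/control 10% | GQ 10%/control 30% |
|---|---|---|---|
| 0 (control flat) | -0.425 | -0.388 | -0.463 |
| -0.25 | -0.425 | -0.350 | -0.500 |
| -0.6 | -0.425 | -0.298 | -0.553 |
| +0.5 (GQ flat, control worsens) | -0.425 | -0.463 | -0.388 |

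Equal drop-out or a flat control arm pulls the Week-12 effect toward the null. At GQ 10%/control 30%, LOCF exaggerates only if the common improvement exceeds 0.25 SD (0.15 x |C| > 0.075 x 0.50).

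Week 16 can differ. In a simulation where the benefit fades to -0.10, LOCF gave -0.11 to -0.15 with a flat control arm, because earlier and better scores are carried forward.

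**Cortisol**

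With two time points, only baseline can be carried to Week 12. If muT and muC are the true mean changes,

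LOCF difference = (1 - dT)muT - (1 - dC)muC.

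- 20% missing in each arm: 0.8(muT - muC), a 20% shrinkage. For example, -0.50 becomes -0.40.
- muT = -0.5, muC = -0.3 (true difference -0.20): GQ 30%/control 10% gives -0.35 + 0.27 = -0.08; GQ 10%/control 30% gives -0.45 + 0.21 = -0.24.
- The imputed zeros also shrink the SD of change. With a true SD of 1 and 20% missing, it becomes sqrt(0.8) = 0.89 when the mean change is 0, and sqrt(0.8 x 1.25 - 0.4^2) = 0.92 when it is -0.5. This feeds the t test and the denominator of Cohen's d.

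In simulated trials of 30 per arm with both arms changing by -0.5 and 30%/10% loss either way, LOCF gave about +/-0.10 and rejected 7.0% of the time. Analysis of observed data gave about 0.00 and 5.0%.

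**The case against.** The primary outcome is feasibility, and LOCF does not enter it. Missing data are themselves a feasibility outcome, and drop-outs are recorded with reasons. All of this stands, and it lowers the severity.

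The unequal splits and the 0.6 SD trend are assumed. The Background says fatigue is more prevalent within six months of treatment, but it also says fatigue can persist for years. That does not establish improvement over 12 weeks. The practical harm can be modest: 0.09 SD is about 0.4 of a standard error (0.894 x sqrt(2/30) = 0.23 at a within-person correlation of 0.6), and the false-positive rate in the case above rose only to 7.0%. These limits also stand.

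A reader might go further in three ways that the documents do not support:
- **That the arm losing more participants alone decides the direction, or that LOCF will favour GQ.** The table shows that trajectories matter as much, and that the Week-12 bias is often toward the null.
- **That every incomplete urine collection becomes a zero change.** The cortisol section can be read as leaving such samples out, and an inadequate baseline cannot be filled by LOCF at all.
- **That the mixed model already repairs the problem.** As written it has no group-by-time term and may be fitted to carried-forward data.

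Sensitivity analyses are commonly left to an analysis plan, so their absence here is no fault. LOCF is different: it is a stated choice that a later document would have to contradict.

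**Conclusion.** The concern holds for the secondary outcomes and should be fixed. LOCF is biased here even when data are missing completely at random. Under the assumed scenario, a true -0.50 SD is estimated at anywhere from about -0.30 to -0.55 depending on the drop-out split, and a true zero at up to about 0.09 SD either way. These sizes depend on the assumed trajectories, timing and splits; that bias arises whenever outcomes would have gone on changing does not.

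For cortisol, the zero change is conditional on LOCF being applied to a participant with a valid baseline and no Week-12 value. The 20% shrinkage assumes 20% missing at random in each arm; the documents give no rate of unusable samples. The inadequate-sample rule and the blanket LOCF rule must be reconciled. The feasibility conclusions are not affected.

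**What to change.** 1. Delete LOCF. Fit the planned mixed model by likelihood to all observed visits of all randomised participants, without imputation.
2. Specify group, time and group-by-time as fixed effects, with a participant random effect or a within-person covariance. Removing LOCF alone is not enough, because the model as described yields no Week-12 treatment contrast.
3. Analyse Week-12 cortisol on observed data with baseline adjustment. State how inadequate samples are treated, so that the cortisol and analysis sections agree, and report missing and inadequate samples by arm.
4. Add one missing-not-at-random sensitivity analysis, by delta-adjusted or reference-based multiple imputation.

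The cost is a change of wording and a little extra analysis; trial conduct does not change. The main analysis would then rely on missing at random, which illness-related drop-out may strain, and item 4 is there to test that.

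### None of the analyses stated for fatigue, sleep, depression and cortisol adjusts for the Week-1 value the trial already plans to collect, which costs precision on the secondary outcomes

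*Protocol article*

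**What the plan says.** Under Quantitative Data the article makes three statements about comparing the arms.

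- A general one: "Between group comparison will be conducted using the t test, chi-square test, or Fisher exact test, as appropriate". It does not say which variables the t test covers, at which visit, or whether on scores or changes.
- A generalized linear mixed model whose outcomes are BFI, PSQI, CES-D and 24-hour urine cortisol. Treatment group is the fixed effect and time the random effect. No baseline covariate and no group-by-visit term is stated.
- Cohen's D, whose definition includes "mean change in the variable divided by pooled variance of the change".

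On the data available, Study Assessments states: "Secondary patient-reported outcomes on fatigue, depression, and sleep will be measured at baseline (Week-1", with later measurements at Weeks 6, 12 and 16. Cortisol is planned at Week-1 and Week-12, but the cortisol section records no value when a 24-hour collection is incomplete. Randomization and Blinding specifies minimization at 1:1 and names no balancing factors. Feasibility is the primary outcome, so these four outcomes are secondary.

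**The concern.** A participant's own Week-1 score is usually a strong predictor of the later score. Leaving it out of a comparison of follow-up scores ignores that information. Subtracting it, as a change score does, fixes the slope on baseline at 1 and over-corrects whenever the true slope is lower. The stated mixed model has no baseline term, so it does not fill the gap.

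Two things are at stake. The estimates are less precise than the same data allow, in a trial of only 60. They also shift with whatever baseline difference chance produces, and a follow-up comparison and a change score shift in opposite directions. A reported test and a reported Cohen's D could then disagree for no reason connected with the intervention.

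**Working it through.** **The plan's own figure.** Sample Size says "the sample size is 25 cases in each group with 90% power and two-sided 5% significance trial design", starting from "Using a small effect size (0.2") "rather than a medium effect size (0.5"). A direct two-group comparison at d = 0.2 needs 2 × ((1.960 + 1.282)/0.2)² ≈ 526 per arm, so 25 is not reproduced. The source cited for it is not at hand, and that is a separate point. Only the effect sizes 0.2 and 0.5 are used below, as reference values.

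**Inputs.**
- Two-sided 5% (Sample Size). Quantitative Data adds: "We will report the results for two-sided 5% tests for the primary trial outcome".
- n = 30 per arm: 60 randomized 1:1, analysed by intention to treat with last observation carried forward.
- Baseline to follow-up correlation r: not in the article. Assumed 0.3 to 0.7, with equal SDs at both times.
- Minimization assumed not to balance baseline scores, since no factors are named.

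**Precision.** The variance V of the group contrast, relative to a follow-up-score comparison, is 1 for follow-up scores, 2(1 − r) for change and 1 − r² with baseline adjustment. The information lost against adjustment is 1 − (1 − r²)/V. That equals r² for follow-up scores and (1 − r)/2 for change.

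| r | V, follow-up | V, change | V, adjusted | Loss, follow-up | Loss, change |
|---|---|---|---|---|---|
| 0.3 | 1 | 1.40 | 0.91 | 9% | 35% |
| 0.5 | 1 | 1.00 | 0.75 | 25% | 25% |
| 0.7 | 1 | 0.60 | 0.51 | 49% | 15% |

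At r = 0.5 the loss is equivalent to 0.25 × 60 = 15 participants.

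**Chance imbalance.** The standard error of the baseline mean difference is √(2/30) = 0.258 SD. Given a baseline difference B, the expected follow-up difference moves by rB and the expected change difference by −(1 − r)B. For B of one standard error:

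| r | Follow-up score | Change score |
|---|---|---|
| 0.3 | +0.08 SD | −0.18 SD |
| 0.5 | +0.13 SD | −0.13 SD |
| 0.7 | +0.18 SD | −0.08 SD |

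**Power.** Noncentral t with noncentrality (d/√V) × √(n/2), 58 degrees of freedom unadjusted and 57 adjusted. At d = 0.5 and r = 0.5:
- Follow-up or change: 0.5 × √15 = 1.94, power 47.8%.
- Adjusted: (0.5/√0.75) × √15 = 2.24, power 59.4%.

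At d = 0.2 and r = 0.5 the same formula gives 11.9% and 14.2%.

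**The mixed model.** The article does not say whether Week-1 is one of the repeated outcomes. If it is, and group is the only fixed effect, the group coefficient averages a visit with no effect and three visits with one. An effect d constant over the later visits is then estimated as (0 + d + d + d)/4 = 0.75d. If Week-1 is not an outcome, it is not used at all. On neither reading is there baseline adjustment.

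**The case against.** The strongest reply is that the article assigns these four outcomes to the mixed model, not to the t test. The t test sentence follows the descriptive summaries and may serve only for simple comparisons, and covariates are often left to an analysis plan. This stands in part. A reader might infer that a t test is certainly the main comparison for fatigue or sleep; the text does not say so, and the follow-up-score figures apply only if one is run. The reply does not reach Cohen's D, where raw change is a stated choice. Nor does it reach the model, whose stated terms include no baseline.

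Other stronger readings are tempting and do not hold:

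- That half the information is wasted. That is close to true only for a follow-up-score t test near r = 0.7. For the change score, the one use the article states, the loss is 15% to 35% over the assumed range.
- That an imbalance as large as the 0.2 effect enters the estimate. The raw one-standard-error imbalance (0.26 SD) exceeds 0.2, but only r or (1 − r) times it is carried through. It would be smaller still if minimization used baseline scores.
- That every participant has a baseline. Incomplete cortisol collections are not recorded.
- That the analysis rests on about 24 per arm. Sample Size does say "Allowing for a drop-out of about 20% based on previous studies", and 30 × 0.8 = 24, but the stated analysis carries the last observation forward, which keeps the set nearer 30. At 24 the comparison is similar: 39.6% against 49.9% power.
- That Cohen's D will be what later trials use. The Conclusion speaks generally of insights guiding future interventions and mentions no effect size.

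It is also fair to say that the secondary outcomes of a feasibility trial do not decide its success.

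**Conclusion.** The point holds as a loss of efficiency: baseline adjustment appears nowhere in the stated analysis of the four outcomes, and adding it is close to free. Under randomization the unadjusted comparisons remain valid on average. A reader might infer an inflated type I error, and that would be wrong. The cost is lost precision and conditional bias on secondary outcomes.

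The size depends on r, which the article does not give. Adjustment has the lower variance at every r strictly between 0 and 1, apart from one degree of freedom, so the direction does not depend on the assumption. It does not rescue power at the 0.2 effect named under Sample Size, where power stays below 15% at r = 0.5. The change is worth making, but the trial's primary feasibility aim does not depend on it.

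**What to change.** For each of the four outcomes, name one baseline-adjusted analysis as the between-group comparison, in place of the t test.

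- **BFI, PSQI, CES-D:** the mixed model on Weeks 6, 12 and 16, with group, visit and group-by-visit as fixed effects, the Week-1 score as a covariate and a participant random effect. Report the Week-12 difference with its confidence interval.
- **Cortisol:** ANCOVA of the Week-12 value on arm and the Week-1 value. A participant without a Week-1 value could not enter a change score either.
- **Cohen's D:** take the numerator from the adjusted difference and divide by a pooled SD, saying which SD. The present definition divides by a variance, so the result is not in SD units.
- **t, chi-square and Fisher tests:** keep them for variables with no baseline value.

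Using one model per outcome, and not an ANCOVA beside the existing mixed model, avoids two competing estimates of the same effect. The cost is a few sentences in the analysis section, with no new data, visits or staff.

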**Methods::**

This is an open-label randomized controlled trial with 60 participants divided into 2 study groups in a 1:1 ratio. The intervention group will receive 12 weeks of Guolin Qigong intervention with a 4-week follow-up while control will receive usual care under waitlist. The primary outcome will be feasibility measured based on recruitment and retention rates, class attendance, home practice adherence, nature, and quantum of missing data as well as safety. The secondary subjective outcomes of fatigue, sleep quality and depression will be measured at Week-1 (baseline), Week-6 (mid-intervention), Week-12 (post-intervention), and Week-16 (4 weeks post-intervention) while an objective 24-hour urine cortisol will be measured at Week-1 (baseline) and Week-12 (post-intervention). We will conduct a semi-structured interview individually with participants within 3 months after Week-16 (4 weeks post-intervention) to obtain a more comprehensive view of practice adherence.

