The F2F GQ class will be taught by qualified GQ instructors who are both long-term cancer survivors with more than 20 years of GQ training experience to ensure the full potential of the GQ intervention. The Researcher, who is a registered Chinese Medicine practitioner in Malaysia and Australia with more than 20 years’ experience in Qigong, will be in attendance during the F2F GQ class to ensure the safe and seamless facilitation of the training session.

Home practice is recommended for non-class days according to individual health status and available time.^
54
^ Participants will be provided with class notes and video links (Supplemental Material 3) to promote and support home practice. Home practice after the intervention period is encouraged for incorporation into daily life to foster a healthy lifestyle.

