#### Feasibility outcomes

Feasibility will be assessed based on recruitment rate, retention rate, class attendance, home practice adherence, the nature and extent of missing data, and safety. Safety will be monitored and assessed based on total number of Adverse Event and the presence of any Serious Adverse Event.^
75
^

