### Trial Monitoring

The Researcher will report progress of the trial to the panel of supervisors on a quarterly basis. Annual reports will be submitted to the human ethics committee to monitor the trial progress and outcomes. Participants in the GQ group will be advised to record any perceived adverse events in the practice diary and this will be recorded in participants’ Adverse Event Form by the Researcher. The severity, expectedness and causal relationship with GQ intervention will be assessed for every adverse event according to guidelines for safety reporting.^75,87^

The schedule of the enrollment, intervention, and data collection is shown in Figure 2.

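### The primary outcome, feasibility, is assigned two-sided 5% tests that do not address its absolute targets, and those targets are ranges without one pass mark

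*Protocol article*

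**What the plan says.** The abstract defines the primary outcome: "The primary outcome will be feasibility measured based on recruitment and retention rates, class attendance, home practice adherence, nature, and quantum of missing data", together with safety. The Feasibility outcomes section repeats this: "Feasibility will be assessed based on recruitment rate, retention rate, class attendance, home practice adherence, the nature and extent of missing data, and safety". The hypotheses at the end of the Background give numerical targets for two of these components: "Feasibility of this study is established at about 80% to 85% retention rate and 75% to 85% class attendance rate".

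Under Quantitative Data the plan states: "We will report the results for two-sided 5% tests for the primary trial outcome". The tests named in that section are between-group ones: "Between group comparison will be conducted using the t test, chi-square test, or Fisher exact test, as appropriate". The mixed model there is confined to the fatigue, sleep, depression and cortisol outcomes, all of them secondary. The section also provides a descriptive summary: "Categorical data will be summarized as counts and percentages of each category".

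On adverse events, Trial Monitoring says: "Participants in the GQ group will be advised to record any perceived adverse events in the practice diary". Study Assessments and Data Collection also describe adverse event recording, but neither limits it to one arm.

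**The concern.** A feasibility outcome with absolute targets is a question of estimation: what proportion stayed, what share of classes was attended, and is that enough. A significance test needs a null value, and none is given for any feasibility measure. The tests that are named take equality of the arms as their null, which is not the feasibility question.

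The targets raise a second difficulty. Each is a range, and the article does not say which end is the criterion. The plan allows for about 20% drop-out, which corresponds to the bottom of its own retention range, so a result near the boundary is quite possible. The pass mark should therefore be settled before the data are seen.

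At stake is the headline conclusion of the trial. A p-value attached to the primary outcome could be read as evidence for or against feasibility when it is neither. The secondary analyses are not affected.

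**Working it through.** **Inputs.** 60 randomised, 30 per arm, drop-out about 20% (Sample Size). Retention target about 80% to 85%, attendance target 75% to 85% (Background). Two classes a week for 2 weeks, then one a week for 10 weeks (Guolin Qigong). Controls are offered the classes after Week 16 (Usual Care Waitlist Control).

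**The plan's own figures.** 25 × 1.2 = 30 per arm, or 60 in total, as stated. A 20% loss means 80% retention, or 48 of 60. Classes: 2 × 2 + 10 × 1 = 14. The attendance range is then 0.75 × 14 = 10.5 to 0.85 × 14 = 11.9 classes.

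**Step 1: which components can be tested between groups?**

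| Component | Data in both arms during the comparison? | Does a between-group test address the target? |
|---|---|---|
| Class attendance | No, GQ only | No comparator |
| GQ home practice | No, GQ only | No comparator; no target stated |
| Retention | Yes | No: it tests equality, not 80% to 85% |

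**Step 2: what would the retention test deliver?** Normal approximation, power = Φ((d − 1.96·se0)/se1), with p1 = 0.85, p2 = 0.80, n = 30 per arm and d = 0.05.
- Pooled proportion 0.825; se0 = √(0.825 × 0.175 × 2/30) = 0.0981.
- se1 = √(0.85 × 0.15/30 + 0.80 × 0.20/30) = 0.0979.
- Power = Φ((0.05 − 1.96 × 0.0981)/0.0979) = 7.3%. For 95% against 80% the same formula gives 41.7%.

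Two invented results show that the test and the target can disagree:
- 18/30 retained in each arm is 60% retention and no difference at all: non-significant, target missed.
- 30/30 against 24/30 has a two-sided Fisher p of 2 × C(30,6)/C(60,6) = 2 × 593,775/50,063,860 = 0.024: significant, although both arms are at or above 80%.

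**Step 3: how much does the choice of mark matter?** X ~ Binomial(60, p). An 80% mark needs X ≥ 48 and an 85% mark needs X ≥ 51.

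| True retention (assumed) | P(X ≥ 48) | P(X ≥ 51) |
|---|---|---|
| 75% | 23.2% | 4.5% |
| 80% | 57.6% | 21.3% |
| 82.5% | 75.8% | 38.0% |
| 85% | 89.4% | 58.8% |

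At 82.5%, the chance of 48 to 50 retained, where the two marks disagree, is 75.8 − 38.0 = about 38%.

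**Step 4: precision (exact Clopper-Pearson 95% intervals).** 48/60: 67.7% to 89.2%. 51/60: 73.4% to 92.9%. One arm, 24/30: 61.4% to 92.3%.

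**The case against.** The case for the plan is that it does provide what is needed. Counts and percentages are planned, drop-out and its reasons are recorded in both groups, targets are given, and interviews will add evidence on acceptability. The between-group tests are to be used only where appropriate, so nobody is directed to test class attendance against an arm that has no classes. The sentence about 5% tests does not itself say that they are between-group. All of this stands, and it limits the point. It does not remove it: the sentence assigns tests to the primary outcome, supplies no null value, and sits beside between-group tests only.

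Several stronger readings are tempting, and the document does not support them.
- *The trial cannot say whether GQ is feasible.* A reader might infer this, but the descriptive rates can be set against the targets without any p-value.
- *Retention of 82% could be declared a failure.* It lies inside the range that the Background calls feasible, and nothing makes 85% a minimum. The fair point is that one mark should be stated. The contrast of 58% with 21% shows what the ambiguity could cost; it does not show that 85% is an intended mark.
- *Adverse events are recorded in the GQ arm only.* Trial Monitoring gives an explicit route for that arm alone, but Study Assessments and Data Collection are not arm-specific. Whether control events are recorded in the same way is unclear. Trial Monitoring also provides for an assessment of each event's causal relationship to GQ. That addresses relatedness, though it does not supply a comparator.
- *Home practice has no denominator.* The protocol says: "Home practice is recommended for non-class days according to individual health status and available time". Non-class days can be counted: 12 × 7 − 14 = 70 over 12 weeks. A target or fuller definition may be in the full protocol or analysis plan, and its absence from an article is not a finding.

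**Conclusion.** The point holds in a limited form. The tests assigned to the primary outcome do not answer the feasibility question, and the criterion is stated as a range. For attendance and home practice the named tests have no comparator. For retention they have about 7% power for a five-point difference, and neither a significant nor a non-significant result shows whether the target is met. The choice between the two ends of the retention range moves the chance of passing from 58% to 21% if true retention is 80%.

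The 80% is an assumption taken from the drop-out allowance, which is a planning figure and not a forecast; the table shows the range from 75% to 85%. The binomial figures assume that participants drop out independently and that all 60 randomised form the denominator. Adverse event recording is a matter for reconciliation and has no bearing on a verdict about retention or attendance. The correction should be made, and it is nearly free.

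**What to change.** 1. Under Quantitative Data, replace the sentence on 5% tests for the primary outcome with: *Feasibility rates will be reported overall and, where defined, by arm, with 95% confidence intervals (exact for proportions) and no between-group hypothesis test.*
2. In the Background, state the lower figures as the minimum criteria, fixed before analysis: at least 80% of all randomised participants retained at Week 16, and mean attendance of at least 75% of the 14 classes in the GQ arm. This keeps the plan's own numbers and leaves 80% to 85% retention counted as feasible. The denominator should be all randomised because the Intervention section lets participants opt out after learning their allocation.
3. Reconcile Study Assessments, Trial Monitoring and Data Collection on whether adverse events are recorded in both arms. If control events are not recorded in the same way, make no between-arm safety comparison.

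The cost is wording only, with no new data collection. There will be no p-value for the primary outcome, and the intervals will be wide: 48/60 gives 68% to 89%. A fixed mark does not remove sampling error either, since with true retention of 75% the trial would still reach 48 of 60 about 23% of the time. The interval should therefore be reported beside the verdict.
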